### 17.3.5 Immunology

Antibody levels in these samples will be analysed in relation to (i) the relative effect of the two different interventions on the development of general and pregnancy-specific immunity to *P. falciparum* malaria, and (ii) in multivariate analyses, in relation to pregnancy outcomes, to ask whether antibody level at enrolment predicts which women will respond best to IPTp or to ISTp. We will specifically ask whether immunity correlates with decreased risk of recurrent infection (recrudescence or reinfections), and with better pregnancy outcomes (birth weight, haemoglobin). In some models antibody response will be entered as the dependent variable, with treatment groups as exposure variable and other variables such as gravidity and age as covariates. In other models baseline antibody levels will be independent variables to determine if they are predictive of treatment outcome (e.g. birth outcome/placental infection etc) and if pre-existing malarial immunity is a potential effect modifier of treatment effect.

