| HIV**                                                 |                                   |                                        |                                                                   | X**                                       |                                            |                                        |                                           |          |                                   |                                        |
| Blood markers of malaria immunity and iron deficiency | X                                 |                                        |                                                                   |                                           |                                            |                                        |                                           | X        |                                   |                                        |

\*Women in the ISTp-DP group who were RDT-positive and treated with DHA-PQ

\*\*Routine care

An ultrasound scan will be done at screening, enrolment, or within a month of enrolment.

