#### 16.1.2 Baseline assessment

A baseline assessment will be conducted for each participant comprising demographic information, socioeconomic information, insecticide treated net (ITN) and indoor residual spraying use, medical and obstetric history, and clinical assessment. Any relevant information already collected during the screening process or at previous antenatal appointments for the same pregnancy will be copied from the antenatal cards onto the CRF, so that questions, tests and examinations are not unnecessarily duplicated.

Study-relevant information recorded at the first visit will include age; area of residence; prior use of ITNs; number of previous known pregnancies and number of previous births. Clinical assessment will include height and weight, fundal height, reported date of last menstrual period and estimated gestation.

A 5 ml venous blood sample will be taken and used for both routine and study-specific testing. This will be obtained after consent for eligibility screening has been obtained but before consent for enrolment in the trial; women who have not been tested for HIV in their current pregnancy will be tested for HIV, and all women will be tested for anaemia and haemoglobin levels. Women not previously tested for syphilis in this pregnancy will be tested and treated if positive. The same blood sample will be prepared for later study-specific testing for malaria (blood smear microscopy and PCR), for markers of immunity to *P. falciparum* malaria, and for markers of iron deficiency. Aliquots of separated blood plasma will be stored at -20 or -80C for immunity studies. A filter-paper sample will be prepared and stored for future research if the woman has given her consent for this.

If not already done, an ultrasound scan will be done at this visit or at a separate visit within a month of enrolment.

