#### **16.4.4 Additional study-specific testing**

All consenting participants will have venous blood samples taken, prepared and stored for later malaria testing using standard microscopy of blood smears and PCR of dried blood spots. Testing will be done blindly and results will not be made available to study staff until the end of the trial.

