### **16.8.1 Peripheral blood sampling**

A 5 ml venous blood sample will be taken from the mother and tested for malaria using RDT, standard microscopy and PCR; and tested for Hb concentration using hemocue. Women found to have malaria infection by RDT or microscopy, or anaemia ( $\text{Hb} \leq 11 \text{ g/L}$ ) will be treated as appropriate. This sample will also be used to test for markers for general and pregnancy-specific immunity to malaria, and for markers of SP resistance and iron deficiency.

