## 17 Statistical methods

### 17.1 Sample size

The trial will use a stratified design with one strata for primigravidae and secundigravidae and one strata for multigravidae. It is designed to detect a 25% reduction (RR 0.75) in composite adverse birth outcomes (SGA, low birth weight and pre-term birth) in women in their first and second pregnancies with an 90% power and a 2-sided significance level of 0.05, if the rate of placental malaria in the IPT-SP group is similar to that found ongoing observational studies of women receiving routine care in the same area of Malawi. The proposed difference is based on four previous trials of IPTp which jointly reduced low birth weight by 29%. Thus the efficacy of ISTp is expected to be similar to the efficacy of IPTp before the emergence of widespread SP resistance. In the ongoing IPT-mon study in Malawi, the incidence of SGA, low birth weight or preterm birth was 40.3% (N=494) ([name], personal communication). Therefore the study is designed to detect a 25% difference between 40.3% in the control (IPTp) group and 30.2% in the intervention (ISTp) group.

This would require 491 participants in each arm or 982 in total. To allow for a 15% loss to follow-up, 1155 women in their first and second pregnancies will be recruited. This sample size would also have an 81% power to detect a 25% or greater reduction in placental malaria (active or past infection), with a significance level of 0.05. If a power of 80% is used, the study can detect a difference of 21.8% or greater in the primary endpoint. If the incidence is 33.3% instead of 40.3% the study still has 80% power (instead of 90%) to detect a 25% reduction.

The trial is also designed to detect a 50% reduction in past or present placental malaria infection at delivery in multigravidae, based on previous studies of IPTp, assessed by placental histopathology and RDT. The current rate in women in Malawi who are taking IPTp-SP is estimated from IPT-mon at 20.5% ([name], personal communication). A reduction by 50% to 10.25% will require 213 women per arm or 426 in total. To allow for a 15% loss to follow-up we will recruit 500 multigravidae.

The total sample size will therefore be  $1155 + 500 = 1655$ .

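### The model comparing antibody response between arms (section 17.3.5) does not name the woman's own enrolment antibody level as a covariate, so a nearly free gain in precision is left unspecified

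*Combined protocol and SAP*

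**What the plan says.** Section 17.3.5 (Immunology) describes two families of models. In the first, antibody response is the dependent variable, "with treatment groups as exposure variable and other variables such as gravidity and age as covariates". The second uses the enrolment measurement: "In other models baseline antibody levels will be independent variables to determine if they are predictive of treatment outcome", with birth outcome and placental infection as the examples of outcome. The section does not define antibody response, does not say which visit supplies it, and gives no term for repeated samples from one woman.

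The enrolment value will exist. Section 16.1.2 says of the baseline sample: "Aliquots of separated blood plasma will be stored at -20 or -80C for immunity studies". Section 16.8.1 says of the delivery sample: "This sample will also be used to test for markers for general and pregnancy-specific immunity to malaria".

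The documents differ on a third sample. In the visit table (section 3.2), the Immunology row is marked at booking, final antenatal visit and delivery. A second row, "Blood markers of malaria immunity and iron deficiency", is marked at booking and delivery only. Section 16.4.4 describes the study-specific blood at the final antenatal visit as "prepared and stored for later malaria testing using standard microscopy of blood smears and PCR of dried blood spots" and does not mention immunology.

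Objective 6.2.4 is worded as exploratory.

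**The concern.** The question put to these data is whether immunity develops differently under the two strategies. Women start at different levels, which depend on past exposure and gravidity, and much of the spread at delivery may simply carry that over. The woman's own enrolment level is the measurement most directly able to remove this spread. The plan collects it and uses it as a predictor elsewhere, but does not name it in the one model that compares antibody between arms.

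Precision is at stake, not validity. Randomization keeps an unadjusted comparison of one follow-up value per woman unbiased. If the enrolment level predicts the follow-up level, leaving it out widens the confidence interval for no saving. The sample size was set for birth outcome and placental infection, so nothing shows that the antibody comparison has precision to spare.

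**Working it through.** **1. The plan's own figures.** Section 17.1 sizes the trial for its two primary endpoints only. No sample size, standard deviation or correlation is given for antibody.

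First and second pregnancies: 40.3% against 0.75 x 40.3% = 30.225%, "with an 90% power and a 2-sided significance level of 0.05".
- n = [1.96 sqrt(2 p q) + 1.2816 sqrt(p1 q1 + p2 q2)]^2 / (p1 - p2)^2, where p is the mean of p1 and p2, and q = 1 - p
- this gives 471 per arm, and 491 with continuity correction, which matches the stated 491.

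Multigravidae: 20.5% against 10.25%. At 80% power (the section states none for this stratum), the same method gives 194 per arm, and 213 with correction, which matches the stated 213.

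These figures are the most evaluable women the antibody comparison could have under the planned 15% loss. Storage and transport of blood need separate consent (section 11), so the real number may be lower.

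**2. Gain from adjusting for the enrolment level.** Let rho be the correlation between enrolment and follow-up antibody levels that remains after gravidity and age. The documents give no value; 0.3 to 0.7 is assumed.
- Variance of the treatment difference, adjusted / unadjusted = 1 - rho^2.
- Power of a contrast that has 80% power unadjusted = Phi((1.96 + 0.84) / sqrt(1 - rho^2) - 1.96).
- Detectable difference at 80% power, in SD units = 2.80 x sqrt(2 (1 - rho^2) / n).

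| | Unadjusted | rho 0.3 | rho 0.5 | rho 0.7 |
|---|---|---|---|---|
| Variance | 100% | 91% | 75% | 51% |
| Power | 80% | 83.6% | 89.9% | 97.5% |
| Detectable, 491 per arm | 0.179 | 0.171 | 0.155 | 0.128 |
| Detectable, 213 per arm | 0.272 | 0.259 | 0.235 | 0.194 |

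**3. Check by simulation.** With 491 per arm, 2,000 runs and no true effect, the mean standard error fell from 0.0638 to 0.0553 at rho 0.5. The variance ratio is (0.0553 / 0.0638)^2 = 0.75. At rho 0.7 it fell from 0.0638 to 0.0456, a ratio of 0.51. At these two correlations the false-positive rates were 0.060 and 0.059 unadjusted, and 0.056 and 0.052 adjusted. The simulation error is about sqrt(0.05 x 0.95 / 2000) = 0.005, so all are compatible with 5%, the unadjusted analysis included.

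**4. If antibody response means change from enrolment.** With equal variances at the two visits, the variance of a change score relative to the unadjusted level is 2(1 - rho): 140% / 100% / 60% at rho 0.3 / 0.5 / 0.7. It exceeds the adjusted variance by 2(1 - rho) - (1 - rho^2) = (1 - rho)^2, which is never negative. On that reading too, naming the enrolment level as a covariate does at least as well.

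**The case against.** **The list is open.** Gravidity and age are introduced as examples, and the section speaks of some models, not one fixed model. A reader might infer that the plan excludes the enrolment level. It does not; it leaves it unspecified. Antibody response could also mean change from enrolment, which would already use the paired value. This stands: the loss of precision is possible, not certain. It does not remove the case for naming the covariate, because an open list lets the choice be made after the data are seen, and a change score is no more precise than covariate adjustment (step 4).

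**Baseline imbalance is covered.** Section 17.3.2 promises to take imbalance into account. Its examples do not include antibody level, and the purpose here is precision whether or not the arms are balanced.

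**Pooling of samples.** A reader might go further and infer that a woman's samples will be analysed as independent records, which would make the confidence intervals too narrow. With k pooled samples per woman, the nominal 5% error would become 2(1 - Phi(1.96 / sqrt(1 + (k - 1) rho))): 9% to 13% for k = 2 and 12% to 21% for k = 3, over the same range of rho. The documents do not support that reading. Nothing in them says samples will be pooled, and the problem does not arise with one value per woman. The third sample rests on one table row that another row and section 16.4.4 do not match. What remains is a request to say what happens if two follow-up samples are analysed together.

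**The analysis is exploratory.** No decision rule or error rate is attached to it, so the stakes are low. That stands, and it sets the weight of the point.

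**Conclusion.** The point holds as a minor, low-cost improvement. Section 17.3.5 does not name the woman's enrolment antibody level in the model comparing antibody response between arms, although the level will be measured and the objective concerns the development of immunity.

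Naming it would cut the variance of the treatment difference by 9% / 25% / 49% at rho 0.3 / 0.5 / 0.7, and raise 80% power to about 84% / 90% / 97.5%. The gain is modest at the low end, under 4 percentage points of power. The size rests wholly on the assumed correlation. The detectable differences also assume that every evaluable woman has an antibody result, so they are best cases.

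An unadjusted comparison at one time point would be valid. The primary endpoints are not touched. The documents do not establish that the enrolment level is ruled out or that any error rate is inflated.

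**What to change.** In section 17.3.5:
- Define antibody response as the level at delivery, and at the final antenatal visit if a sample is assayed there, on a scale suited to each assay.
- Fit an analysis of covariance with treatment, the woman's enrolment antibody level, gravidity group and age.
- If two follow-up samples per woman are analysed together, use a mixed model or GEE with visit and treatment-by-visit terms. Do not enter the enrolment sample as an ordinary post-treatment record. A constrained longitudinal model with a common baseline mean is an acceptable alternative.
- State how a missing enrolment value is handled, since section 17.3.7 gives no method. A missing indicator or mean-imputed baseline is enough in a randomized comparison.

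Reconcile the two immunity rows of the visit table (section 3.2) with section 16.4.4 on whether immunology is sampled at the final antenatal visit.

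The cost is wording only. The adjustment needs no extra women, samples or assays beyond the enrolment measurement already planned. The one small burden is the rule for women without an enrolment value.

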### 17.3.7 Handling of missing data

Every effort will be made to minimize the amount of missing or incorrect data in the trial.

## 17.4 Criteria for early termination of the trial

We will use an adaptive sequential design using one interim analysis half-way for assessing whether to stop the trial early due to safety, efficacy or futility. The Lan-DeMets alpha spending function with O'Brien-Fleming type boundaries will be used to preserve the overall type I error rate for efficacy at the 0.05 level. Interim analyses will be conducted by the independent Data Monitoring Committee (DMC) supported by the trial statistician. The DMC will provide the trial steering committee only with a recommendation to continue, terminate or modify the trial.

## 17.5 CONSORT statement

Reporting of the statistical analysis will comply with CONSORT Guidelines.

## **17.6 Economics and implementability sub-study data analysis and management**

Facility costs data will be collected. Economic datasets will be analysed using STATA, Microsoft Excel and TreeAge Pro.

Quantitative data from surveys and structured observations will be double entered into a database and validated. Qualitative data from FGDs and semi-structured interviews will be recorded electronically, transcribed and entered into N-Vivo or Atlas for extraction of themes.

## **18 Safety reporting**

### **18.1 Definitions of adverse events**

Definitions of different types of adverse events are presented in the Appendix 1.

### **18.2 Reporting procedures for all adverse events**

An independent physician will be appointed by the sponsor (LSTM) to act as a study safety monitor. He or she will be based in Malawi.

All adverse events occurring during the study, observed by the investigator or reported by the participant, whether or not attributed to study medication, will be recorded using Adverse Event Forms. The following information will be recorded: description, date of onset and end date, severity, seriousness and action taken. Follow-up information will be provided as necessary.

The intensity of events will be assessed on the following scale: 1 = mild, 2 = moderate, 3 = severe, 4 = life-threatening, 5 = death

The relationship of adverse events to the study medication will be assessed by a medically qualified investigator and the independent safety monitor. If the safety monitor disagrees with the investigator's assessment, both opinions will be included in the report.

The safety monitor will evaluate the expectedness of each suspected adverse event according to the Summary of Product Characteristics for SP and the Investigators Brochure for DHA-PQ.

Any adverse reactions to the study drugs will be followed-up until resolution or stabilisation to ascertain the final outcome.

The investigator will judge whether or not an adverse event is of sufficient severity to require discontinuation of the study treatment. If this occurs, or if the participant herself wishes to withdraw due to what she considers to be an intolerable adverse reaction, she will be offered an end of study assessment and be given appropriate medical care until symptoms cease or the condition becomes stable. If she agrees she will be continued to be followed up according to schedule.

### 18.3 Reporting procedures for serious adverse events

The investigators will report all serious adverse events (SAEs) that occur in the course of the study to the safety monitor within 24 hours of the investigational site becoming aware of it. All SAEs will be reported, whether or not they are thought to be causally related to the study drugs. All SAEs will be reported using a standard SAE reporting form.

These immediate reports will be followed within the next 24 hours by detailed, written reports. The immediate and follow-up reports will identify participants by their study ID number.

In case of doubt about whether an event fulfils the criteria of serious, the case will be reported to the safety monitor who will assess whether the event should be reported as an SAE.

All SAEs will be reported by the safety monitor or PI to the sponsor (LSTM Research Office) within 48 hrs of discovery or notification of the event. The sponsor will be responsible for notifying the relevant Ethics Committees and the trial Data Monitoring Committee. Additional information received for a case (follow-up or corrections to the original case) will be detailed on a full report SAE form and emailed to the sponsor within 15 days including a report from the safety monitor. This information will be reviewed by the Data Monitoring Committee to consider any action that may be needed in response to reported adverse events.

#### 18.4 Reporting of SAEs and AEs to the Malaria in Pregnancy Consortium

This study is conducted under the auspices of the Malaria in Pregnancy (MiP) Consortium which conducts treatment and prevention trials in 17 other malaria endemic countries (14 in Africa). All anonymized SAE reports and aggregated reports of adverse events will be reported to the secretariat of the safety working group of the Malaria in Pregnancy Consortium based at the Liverpool School of Tropical Medicine. The secretariat collates all SAE and AE reports from each of the trials for review by an Independent Safety Panel of the MiP Consortium that will meet at regular intervals (at least yearly) to review all SAEs reported for the different drugs used to treat and prevent malaria in pregnancy in the second and third trimesters of pregnancy as part of the ongoing trials. This will include prospective information from 860 other women treated with DHA-PQ (Zambia, Ghana, Burkina Faso, and Malawi (Chikwawa district hospital)), 860 women treated with amodiaquine artesunate, 1100 women treated with Coartem, and 1300 with mefloquine-artesunate, as part of other treatment trials, and information on approximately 7000 women treated with SP as part of IPTp.

The Independent Safety Panel consists of six members who are impartial and independent to the studies. It includes people with expertise in statistics, perinatal epidemiology, pharmacology, teratology/toxicology, pharmacovigilance, ethics and trials in developing countries. If so requested by the Data Monitoring Committee of individual trials, the Independent Safety Panel is able to provide advice to them.

## 19 Quality assurance procedures

The study will be conducted in accordance with the current approved protocol, ICH GCP, relevant regulations and standard operating procedures. Regular monitoring will be performed according to ICH GCP.

The Research Support Centre of the College of Medicine will provide the clinical monitoring on behalf of the sponsor. Prior to participant enrolment, the monitor will visit the study sites to assess the adequacy of the facilities, review the protocol and data collection procedures and discuss the responsibilities of the investigator and other study site personnel. The monitor will also make a visit shortly after the start of enrolment, and at periodic intervals during the trial, to ensure that it is being conducted according to the published protocol and any amendments.

The trial Data Monitoring Committee will meet at least annually, with additional meetings being held if there are any specific issues arising.

Direct access to the trial source data will be granted to authorised representatives from the sponsor, host institution and the regulatory authorities to permit trial-related monitoring, audits and inspections. This will be explained to the participants on the consent form or participant information sheet.

